### Day -35 to -1: Screening Period

Informed consent for the study will be obtained prior to any study specific procedures.

At screening, the following procedures will be performed:

- Signed informed consent
- Medical History (including HIV-specific and TB history);
- Previous and concomitant medication history (including a complete history of all anti-retroviral treatments taken by the subject as far as possible)
- Complete physical examination including height and weight;
- Vital signs after 5 minutes in a resting position (seated blood pressure, heart rate, respiratory rate and axillary body temperature);
- Counselling: Pre- & post-HIV test counselling, ARV adherence, risk reduction and the prevention of pregnancy
- Serum  $\beta$ HCG pregnancy test (for all females)
- Standard haematology, clinical chemistry, coagulation and urinalysis assessments (as described in section 6.6.2 )
- Chest x-ray if an x-ray examination performed within 6 months prior to screening is not available to exclude active or acute cardiac or pulmonary disease, including Pulmonary Tuberculosis.
- Thyroid function tests (T4 & TSH)
- CD4+ T cell
- Virological evaluation: HIV-1/HIV-2 ELISA
- HIV-1 plasma viraemia
- Anti-Tat antibodies (IgM, IgG, IgA)
- Assessment of eligibility as per inclusion and exclusion criteria, and results of all assessments performed.

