#### **9.3.1 Assessing Severity**

The safety concepts of "severity" and "seriousness" are distinct concepts. Severity refers to the degree of clinical manifestation. "Seriousness" refers to pre-defined outcomes from an adverse event. A severe adverse event is not always serious and a serious adverse event is not always severe.

For all adverse events the investigator (or qualified designee) is responsible for assessing the severity of the event and the causal relationship of the event to the study vaccine.

The severity of all adverse events, including clinical findings and abnormal laboratory values, will be classified as one of the following grades:

1. Mild
2. Moderate
3. Severe

A Toxicity Table (adapted for this protocol from the Division of Aids table for grading the severity of Adult and Pediatric Adverse Events Version 1.0, December, 2004; clarification August 2009) is provided as an appendix to the protocol for the assessment of severity of specified adverse events. The Toxicity Table Adverse Event Grades do not correlate directly with the classical severity grades of mild, moderate and severe. **For the purposes of recording events in the CRF** Toxicity Table Grade 1 events will be considered mild in severity, Toxicity Table Grade 2 & 3 events will be considered moderate in severity, and Toxicity Table Grade 4 events will be considered as severe.

For adverse events not listed in the Toxicity Table determination of severity requires some level of interpretation as outlined below. The degree of incapacity caused by the adverse event and the level of medical intervention required for treatment may be helpful in assessing the overall severity of the adverse event.

For example:

- Mild events are generally regarded as noticeable but have no impact on normal activities; they may or may not require over-the-counter treatment managed by the subject.
- Moderate events generally have some impact on an individual's normal activities and may require general symptomatic medical intervention by a healthcare professional or by the subject.
- Severe adverse events may be incapacitating, leading to suspension of normal daily activities, and would generally require more immediate medical evaluation and intervention by a healthcare professional.

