### **9.8 Subject Diary and Temperature Monitoring**

Subjects will receive, and be instructed in, the operation of a daily adverse event diary and a thermometer to be used during the 7-day post-vaccination diary period after vaccine administration. The daily adverse event diary is a source document and will record solicited adverse events, daily thermometer assessments of body temperature, and any other adverse events. At the safety visits scheduled 7 days after each vaccination the diary card will be collected and reviewed by the principal investigator (or designee) at which time any clinical details required for complete understanding of the information recorded will be obtained. Diaries not brought to the scheduled visit should be obtained before adverse event assessment can be performed. Lost diaries will be reconstructed as possible on a new diary booklet by the subject from memory at the closest clinic visit and labeled as a reconstructed diary. Adverse events obtained from the diary will be recorded and completely assessed on the Adverse Event CRF. Body temperatures below 38° C will not be considered fevers.

Any change to an AE recorded by the subject on the diary card (e.g., the severity level of an event is changed after interviewing the subject) based on the investigator's evaluation of the event must be explained by notation in source documentation.

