## 20 APPENDIX I: TOXICITY TABLE

This toxicity table has been adapted for Protocol ISS T-003 from the Division of Aids table for grading the severity of Adult and Pediatric Adverse Events Version 1.0, December, 2004; clarification August 2009

| PARAMETER                                                                                        | GRADE 1
MILD                                                                       | GRADE 2
MODERATE                                                                                               | GRADE 3
SEVERE                                                                                        | GRADE 4
POTENTIALLY
LIFE-
THREATENING                                                                                        |
|--------------------------------------------------------------------------------------------------|---------------------------------------------------------------------------------------|-------------------------------------------------------------------------------------------------------------------|----------------------------------------------------------------------------------------------------------|---------------------------------------------------------------------------------------------------------------------------------------|
| SYSTEMIC                                                                                  |                                                                                       |                                                                                                                   |                                                                                                          |                                                                                                                                       |
| Acute systemic allergic reaction                                                                 | Localized urticaria (wheals) with no medical intervention indicated                   | Localized urticaria with medical intervention indicated OR Mild angioedema with no medical intervention indicated | Generalized urticaria OR Angioedema with medical intervention indicated OR Symptomatic mild bronchospasm | Acute anaphylaxis OR Life-threatening bronchospasm OR laryngeal edema                                                                 |

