| Chills                                                                                           | Symptoms causing no or minimal interference with usual social & functional activities | Symptoms causing greater than minimal interference with usual social & functional activities                      | Symptoms causing inability to perform usual social & functional activities                               | NA                                                                                                                                    |
| Fatigue
Malaise                                                                               | Symptoms causing no or minimal interference with usual social & functional activities | Symptoms causing greater than minimal interference with usual social & functional activities                      | Symptoms causing inability to perform usual social & functional activities                               | Incapacitating fatigue/ malaise symptoms causing inability to perform basic self-care functions                                       |
| Fever
(non-axillary)                                                                          | 37.7 – 38.6°C                                                                         | 38.7 – 39.3°C                                                                                                     | 39.4 – 40.5°C                                                                                            | > 40.5°C                                                                                                                              |
| Pain
DO NOT use for pain due to injection (See Injection Site Reactions: Injection site pain) | Pain causing no or minimal interference with usual social & functional activities     | Pain causing greater than minimal interference with usual social & functional activities                          | Pain causing inability to perform usual social & functional activities                                   | Disabling pain causing inability to perform basic self-care functions OR Hospitalization (other than emergency room visit) indicated  |

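### Clinical Grade 3 events are recorded as moderate although Appendix I labels them severe, so the adverse event severity summary merges Grades 2 and 3 and understates absolute severe counts in both arms

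*Protocol*

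**What the plan says.** Section 9.3.1 classifies every adverse event as mild, moderate or severe. For events in the Toxicity Table it sets a conversion for the CRF: Grade 1 is mild, and then "Toxicity Table Grade 2 & 3 events will be considered moderate in severity, and Toxicity Table Grade 4 events will be considered as severe". It introduces this with the remark that "The Toxicity Table Adverse Event Grades do not correlate directly with the classical severity grades of mild, moderate and severe". For events outside the table it gives descriptive guidance, including "Severe adverse events may be incapacitating, leading to suspension of normal daily activities". It ends by stating that the CRF carries only the highest severity level reached during an event.

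Appendix I, the Toxicity Table, heads its columns mild, moderate, severe ("GRADE 3 SEVERE") and potentially life-threatening. A typical Grade 3 entry, used for example for chills and fatigue, is "Symptoms causing inability to perform usual social & functional activities".

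Section 12.7 summarises adverse events by system organ class, preferred term, severity and relationship. It applies Appendix I grading to haematology, clinical chemistry and urinalysis results only.

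On fever, section 9.8 states: "Body temperatures below 38° C will not be considered fevers". The Appendix I fever row starts Grade 1 at 37.7 °C and is restricted to non-axillary readings.

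**The concern.** Safety against placebo is the only secondary objective (section 3), and the severity summary in section 12.7 is where a reader will look for how badly the vaccine is tolerated. Someone who knows Appendix I will take *severe* to mean Grade 3 or worse. Under section 9.3.1 it means Grade 4, plus any unlisted event that the investigator judges severe. A statement that few severe events occurred would then carry much less reassurance than it appears to.

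This is also a rule about what is captured, not only about how it is displayed. If the CRF holds only the three-level term, no later analysis can separate Grade 2 from Grade 3 without returning to source documents. The DSMB's periodic reports of non-serious events (section 10.1) would inherit the same pooling if they are drawn from that field.

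**Working it through.** No stated figure needs reproducing. The check is a comparison of passages with a little arithmetic.

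**1. The two scales side by side**

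| Toxicity grade | Appendix I heading | CRF term under 9.3.1 |
|---|---|---|
| 1 | Mild | Mild |
| 2 | Moderate | Moderate |
| 3 | Severe | Moderate |
| 4 | Potentially life-threatening | Severe |

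The labels agree at Grades 1 and 2 and part at Grade 3. Every listed Grade 3 event therefore moves down one label.

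**2. What falls under moderate as a result (Appendix I)**
- Fever from 38.7 °C to 40.5 °C (Grade 2 is 38.7–39.3, Grade 3 is 39.4–40.5).
- Widespread urticaria, angioedema that needs treatment, and mild symptomatic bronchospasm.
- Ulceration or sterile abscess at the injection site.

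**3. Rows that cannot reach severe.** Where Grade 3 is defined and Grade 4 is marked not applicable, no event can be recorded as severe. Among clinical events these are chills, pruritus associated with injection, and pruritus without skin lesions. Low albumin and random-collection proteinuria share the pattern, but they are laboratory results.

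**4. Listed against unlisted events.** For an unlisted event, section 9.3.1 points to severe when normal daily activities are suspended ("Severe adverse events may be incapacitating, leading to suspension of normal daily activities"). For a listed event, "Symptoms causing inability to perform usual social & functional activities" is Grade 3 and so moderate. The two descriptions overlap, and both kinds of event enter the same table.

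**5. Dilution.** Let a and b be the Grade 3 rates in the vaccine and placebo arms, with a > b, and let g be a common Grade 2 rate. If each subject is counted once at the highest grade, the moderate row compares g + a with g + b. The difference is still a − b, but the ratio (g + a)/(g + b) is closer to 1 than a/b, and the difference has to be seen against a larger background.

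**6. Possible size.** The protocol gives no Grade 3 rate, so the rates below are assumptions. The vaccine arm has 100 subjects (section 5.1.2). The expected number of subjects with a Grade 3 event is 100p, and the chance of at least one is 1 − (1 − p)^100.

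| Assumed p | Expected subjects | Chance of at least one |
|---|---|---|
| 1% | 1 | 63% |
| 3% | 3 | 95% |
| 5% | 5 | 99% |
| 10% | 10 | >99.9% |

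**7. Fever, separately.** The Grade 1 band of 37.7–38.6 °C contains ten tenth-degree values. Three of them (37.7, 37.8 and 37.9) lie below 38 °C, so they are Grade 1 in Appendix I but not fever in section 9.8. Grades 2 to 4 are untouched. The Appendix I row is non-axillary. Clinic visits record "seated blood pressure, heart rate, respiratory rate and axillary body temperature", and section 9.8 does not state the route for the diary thermometer.

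**The case against.** The strongest defence is that the conversion is disclosed. Four grades have to collapse into three terms, section 9.3.1 says openly that the scales differ, and it limits the rule to CRF recording, so a careful reader can decode the tables. That is fair as to transparency. It does not remove the conflict, because Appendix I attaches the very words mild, moderate and severe to Grades 1 to 3.

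Several limits stand:

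- **The functional descriptions are not equivalent.** The guidance on severe also speaks of incapacity and of more immediate medical attention, which resembles Grade 4 wording for fatigue and pain. It overlaps Grade 3 as well as Grade 4, and it is offered as example text for unlisted events.
- **A reader might infer that Grade 3 events disappear.** They do not. Clinical ones are still reported, as moderate, and Grade 3 laboratory results remain visible through Appendix I grading.
- **A reader might infer a bias in favour of the vaccine.** The document does not support that. Assessors are blinded and the same rule applies to both arms.
- **A reader might infer that section 9.8 discards temperatures.** It does not. The diary is a source document that keeps the readings, and clinic temperatures are summarised as vital signs. The rule governs only what is called a fever, and the clash with Appendix I is direct only for non-axillary readings. Three values in ten describes the scale, not the number of fevers missed.
- **The CRF is not shown.** That it holds only the three-level term is an inference from section 9.3.1. A separate grade field, or a table by grade in the SAP, may exist.

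**Conclusion.** The inconsistency is real and is in current text. Sections 9.3.1 and 12.7 together pool listed clinical Grade 3 events with Grade 2, understate the absolute number of severe events relative to the protocol's own Appendix I, weaken the visibility of any Grade 3 excess, and put *severe* out of reach for chills and both pruritus rows. The direction is certain for absolute counts. The amount cannot be computed from the document, and the figures in the table above rest on assumed rates. The conclusion assumes that the severity in section 12.7 is the CRF term defined in section 9.3.1. The mapping does not in itself favour either arm, and it does not touch the primary endpoint.

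The fever mismatch is minor and separate. It is confined to 37.7–37.9 °C and Grade 1, and whether it bites depends on an unstated measurement route.

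**What to change.** - Record the toxicity grade (1–4) on the Adverse Event CRF for every event listed in Appendix I, and state in section 12.7 that clinical adverse events will be tabulated by that grade and arm.
- If a three-level term is kept, make it agree with the Appendix I labels, and bring the guidance for unlisted events into line so that one word has one meaning in the table.
- Reconcile section 9.8 with the Appendix I fever row and state the route of the diary temperature. Which threshold applies is for the sponsor to settle; no view is taken here.

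The cost is one CRF field and a paragraph of text, and the reported number of severe events will look less favourable. If enrolment is already under way and the grade has not been captured, it would have to be filled in from source documents for events already recorded.

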### 9.3.2 Assessing a Causal Relationship (Relatedness)

For all adverse events, the investigator determines a **causal relationship** to the study vaccine without the knowledge of whether the Tat protein vaccine or placebo was administered. A number of factors will be considered in making this assessment, including:

1. the temporal relationship of the event to the administration of the study vaccine
2. whether an alternative etiology has been identified and
3. clinical plausibility.

The investigator will be requested to assess the causal relationship of an adverse event to study vaccine using the following criteria:

| Descriptor | Definition                                                                                                                                                                                                                                                                                                                                                                                                                                                              |
|------------|-------------------------------------------------------------------------------------------------------------------------------------------------------------------------------------------------------------------------------------------------------------------------------------------------------------------------------------------------------------------------------------------------------------------------------------------------------------------------|
| Certain    | The study vaccine is known to be the cause of the adverse event. The evidence establishes a causal relationship; an association exists between the event and receipt of the study vaccine and there is a plausible mechanism for the event to be related to the study vaccine, and causes other than the study vaccine have been ruled out.                                                                                                                             |
| Probable   | It is likely that the adverse event was caused by administration of the study vaccine. The evidence favours acceptance of a causal relationship; an association exists between the event and receipt of the study vaccine and there is a plausible mechanism for the event to be related to the study vaccine, and an alternative aetiology is not apparent.                                                                                                            |
| Possible   | There is a reasonable possibility that the adverse event was caused by study vaccine. There must be a plausible mechanism for the event to be related to study vaccine. The evidence is inadequate to accept or reject, or favours rejection of, a causal relationship; an association exists between the event and the study vaccine but there may also be an alternative aetiology, such as characteristics of the subject's clinical status or underlying condition. |
| Unlikely   | There is less than a reasonable possibility that the adverse event                                                                                                                                                                                                                                                                                                                                                                                                      |

|           |                                                                                                                                                                                           |
|-----------|-------------------------------------------------------------------------------------------------------------------------------------------------------------------------------------------|
|           | was caused by study vaccine                                                                                                                                                               |
| Unrelated | There is no evidence of a causal relationship; another aetiology is known to have caused the adverse event. The alternative aetiology should be documented in the subject's study record. |

The investigator may be assisted by the local medical monitor in determining causality. It is expected that in the event of any uncertainty, communication and consultation may occur in the assessment of the causality of adverse events. Certain, probable and possible are considered to be related. Unrelated and unlikely related are considered to be unrelated.

Every effort should be made by the investigator to determine the existence of any pre-existing conditions that should be taken into consideration when assessing the causal relationship of an adverse event. Pre-existing conditions should be recorded in the CRF as baseline medical history.

#### **9.4 Adverse Event Treatment, Follow-up and Outcome**

Treatment of any adverse events will be determined by the investigator using his/her best medical judgment and according to current clinical practice guidelines. All applied measures as well as follow-up will be recorded in the appropriate CRF. Adverse events will be considered resolved when the condition returns to normal or returns to the subject's baseline status as established on Study Day 0, or when the condition has stabilized with the expectation that it will remain chronic. Since the principal investigator will be blinded for this study, in the event of an emergency where knowledge of the treatment allocation is required for proper clinical management of the subject, the principal investigator may require the un-blinding of the treatment assignment (active treatment or placebo). If possible, sponsor approval should be sought prior to any emergency un-blinding procedure.

The investigator will continue follow-up on adverse events, including clinically significant laboratory abnormalities until the event has resolved, is otherwise satisfactorily explained, or the subject completes the study. If not reported earlier, the outcome of adverse events will be determined when the subject completes the study.

Follow-up for serious adverse events must continue until resolution and the outcome reported to ISS, even if this extends beyond the serious adverse event reporting period (i.e., after the final study visit). For analysis purposes, the outcome for serious adverse events will be determined on the final study visit.

If at any time after completion of the serious adverse event reporting period (the final study visit) the investigator becomes aware of a serious adverse event that is suspected by the investigator to be related to the study vaccine, the event must be reported to ISS.

